## **7.4 Adverse event**

### **Definition of adverse event**

Adverse event (AE) is defined as any untoward medical occurrence in a subject administered the investigational medical product (IMP), which can be manifested as any abnormal sign, symptom, disease, or laboratory finding, and which does not necessarily have to have a causal relationship with investigational drug.

Any untoward medical occurrence from the signing of ICF to the first dose is recorded as medical history. All AEs specified in this protocol that occur after treatment must be completely recorded in the eCRF.

### **Definition of serious adverse event**

Once a subject has been identified as experiencing an AE, the severity of that AE must be assessed. A serious adverse event (SAE) must meet one or more of the following criteria:

1) Death

2) Life threatening

(“Life-threatening” means that the subject is at immediate risk of death at the time of the adverse event, that is, it does not include the adverse event that is assumed to cause death in a more serious form.)

3) Leading to persistent or significant disability or incapacity

4) Resulting in congenital anomalies or birth defects (including those developed prenatally)

5) Other important medical events (IMEs). IMEs may not be immediately life threatening, result in death, or lead to hospitalization, etc., but may, in medical and scientific judgment, endanger the patient/subject or may require intervention to prevent any of the above outcomes. Generally, these events shall also be considered as SAEs. Examples of such events include but not limited to: intensive treatment for allergic bronchospasm in the emergency room or at home; cachexia or convulsions that do not cause hospitalization; drug dependence or drug abuse.

6) A need for hospitalization or prolongation of hospitalization (The patient is hospitalized and meet the criteria for requiring hospitalization even if discharged on the same day. Emergency room visits that resulted in hospitalization also meet the criteria for

requiring hospitalization. However, emergency room visits that do not result in hospitalization do not meet this criterion and should be evaluated for one of the other criteria in this definition [e.g., life-threatening adverse event, important medical event]. Hospitalization for reasons unrelated to the occurrence of the AE [e.g., scheduled or elective surgery for a pre-existing condition that does not worsen or present with unusual/atypical manifestations] is not required to be reported. For example, if a subject develops a condition documented in the medical history and subsequently undergoes a previously planned surgery for that condition, it is not appropriate to record the surgery or hospitalization as a serious adverse event because no adverse event occurs that can be assessed against criteria for seriousness. Note that if a pre-existing condition worsens or shows an abnormal or atypical pattern, it is an adverse event and the seriousness of the event will have to be assessed if necessary.)

#### **Adverse events of special interest**

Adverse events of special interest (AESIs) mainly includes hypoglycemic events and gastrointestinal intolerance reactions (vomiting, nausea, diarrhoea, abdominal pain, constipation, etc.).

#### **Treatment emergent adverse events**

Treatment emergent adverse events (TEAEs): any AE emerging after the first injection of GZR18 or placebo through the end of the safety follow-up period. AEs that occur before dosing of which the severity is increased during the trial are also considered TEAEs.

#### **Definition of suspected unexpected serious adverse reaction**

Suspected unexpected serious adverse reactions (SUSARs): the suspected and unexpected serious adverse reactions whose nature and severity of clinical manifestations are beyond the information available in the Investigator's Brochure for the investigational drug, the Instructions for Use of the marketed drug or the summary of product characteristics.

#### **Judgment of severity of AEs**

The investigator graded the AEs according to the *Common Terminology Criteria for Adverse Events* (NCI-CTCAE) v5.0. AEs not described in the CTCAE v5.0 are classified according to the following criteria:

|          |                                                                                                                                                                          |
|----------|--------------------------------------------------------------------------------------------------------------------------------------------------------------------------|
| Grade 1: | Mild: asymptomatic or mild symptoms; clinical or diagnostic observations only; intervention not indicated.                                                               |
| Grade 2: | Moderate; minimal, local or noninvasive intervention indicated; limiting age appropriate instrumental ADL*.                                                              |
| Grade 3: | Severe or medically significant but not immediately life-threatening; hospitalization or prolongation of hospitalization indicated; disabling; limiting self care ADL**. |

|          |                                                               |
|----------|---------------------------------------------------------------|
| Grade 4: | Life-threatening consequences; urgent intervention indicated. |
| Grade 5: | Death related to AE.                                          |

\*Instrumental ADL refer to preparing meals, shopping for groceries or clothes, using the telephone, managing money, etc.

\*\*Self care ADL refer to bathing, dressing and undressing, feeding self, using the toilet, taking medications, and not bedridden.

#### **Causality determination of adverse drug reactions**

An adverse drug reaction (ADR) is any untoward or unintended reaction possibly related to the investigational drugs in clinical trials. If there is at least a reasonable possibility in the causal relationship between the investigational drugs and the AE, the relatedness cannot be ruled out.

The relatedness between AEs and the investigational drugs are determined according to the following table:

### **Criteria for judgment of relatedness of AEs to investigational drugs**

|                        |                                                                                                                                                                                                                                                                                                                                                                                          |
|------------------------|------------------------------------------------------------------------------------------------------------------------------------------------------------------------------------------------------------------------------------------------------------------------------------------------------------------------------------------------------------------------------------------|
| Definitely related     | The AE follows a reasonable temporal sequence from investigational drug administration, and is a known adverse reaction to the investigational drug, which is alleviated or disappears after drug withdrawal, and reappears after drug re-administration, and cannot be reasonably explained by the subject's existing disease.                                                          |
| Probably related       | The AE follows a reasonable temporal sequence from investigational drug administration, and is a known reaction to the investigational drug, which is alleviated or disappears after investigational drug withdrawal, and cannot be reasonably explained by the subject's existing disease, with unknown effect after re-administration.                                                 |
| Possibly related       | The AE follows a reasonable temporal sequence from investigational drug administration, and is a known or suspected reaction to the investigational drug; however, there may be other factors that may cause the event, such as disease, concomitant medication, etc., and the effect after drug discontinuation is unclear, with unclear information or lack of conclusive information. |
| Unlikely related       | The AE follows a reasonable temporal sequence from investigational drug administration, but the event does not belong to a known type of adverse drug reaction and is most likely caused by the subject's disease or other treatment.                                                                                                                                                    |
| Definitely not related | The AE does not follow a reasonable sequence from investigational drug administration, e.g., the event has occurred before the administration of the investigational drug ; it is not a known adverse drug reaction; or the AE is clearly caused by other factors (e.g., disease of the subject, other treatment, and concomitant medications).                                          |

### **Classification and definition of adverse event outcomes**

- Recovered/resolved: The subject is fully recovered, or the condition is recovered to the level at which the subject participated in the first trial-related activity after signing the ICF by medical or surgical treatment;
- Recovering/resolving: The condition is improving and the subject is expected to recover from the event;
- Resolved with sequelae: The subject has recovered from the disease, but there is a persistent effect from the disease, injury, treatment, or surgery. If sequelae meet the criteria for serious, the adverse event must be reported as serious adverse event;
- Not recovered/resolved: The subject's disease has not improved and symptoms have not changed, or the outcome is unknown at the time of reporting;
- Death: This term is only applicable if the subject dies due to a condition associated with the reported AE. The outcome of other AEs reported of the subject prior to death should be assessed as: "recovered", "recovering", "recovered/resolved with sequela", or "not recovered". AEs with fatal outcome must be reported as serious adverse events;
- Unknown: This term is only applicable if the subject is lost to follow-up.

### **Adverse event reporting**

If reporting SAE, the research center must notify Gan & Lee Pharmaceuticals and its

commissioned CRO within 24 hours of receiving this information. Even if the data is incomplete or more data is clearly needed to draw any conclusions, investigators must still properly fill out the SAE report form provided by Gan & Lee Pharmaceuticals (or its authorized CRO) and submit it to Gan & Lee Pharmaceuticals (or its authorized CRO). Gan & Lee Pharmaceuticals (or its authorized CRO) is responsible for entering the information recorded in this table into the global safety database.

The SAE report form will be provided to the investigators. For investigators, it is important to include an assessment of the causal relationship between SAE and the investigational drug when filling out the SAE report form. The evaluation information of investigators is crucial for Gan & Lee Pharmaceuticals to evaluate the safety of IMP and consider whether it is necessary to accelerate the reporting of SAE to regulatory authorities.

Investigators must report any other information received (such as autopsy or laboratory reports) within 24 hours, and the relevant information must be summarized in the SAE report form.

It is explicitly required that investigators collect any SAE events that occur in each subject within 4 weeks after the first and last administration (even if the investigators determine that these events are not related to IMP), and report them to Gan & Lee Pharmaceuticals (or its authorized CRO). Investigators believe that SAEs related to the investigational drug must be reported to Gan & Lee Pharmaceuticals and its authorized CRO, regardless of the time between the event and the end of the study.

After receiving the SAE report form, Gan & Lee Pharmaceuticals and its authorized CRO will evaluate the expected performance of the SAE report. SAE Expectancy Assessment will be conducted based on IB.

Suspected and Unexpected Serious Adverse Reactions (SUSARs) that are fatal or life-threatening should be reported by the sponsor to the drug regulatory authority and the health care authority as soon as they are first notified, and by the sponsor to all the investigators, institutions, and ethical committees participating in the clinical trial as soon as they are aware of it, and the whole process should not take more than 7 days. And the investigators should improve the follow-up information in the subsequent follow-up (the day of the sponsor's first notification is day 0).

Suspected and Unexpected Serious Adverse Reactions (SUSARs) that are not fatal or life-threatening should be reported by the sponsor to the drug regulatory authority and the health care authority as soon as possible within 15 days of first becoming aware of them, and they should be reported by the sponsor to all investigators, institutions, and ethics

committees participating in the clinical trial. And the follow-up information should be improved in the subsequent follow-up (the day of the sponsor's first notification is day 0).

Other AE information will be summarized in the Development Safety Update Report (DSUR) and submitted to regulatory authorities within the time limit specified by relevant regulations along with the DSUR.

| Reporting of serious adverse events (24 h) |                                                                                                                                                                                                                                                                                               |
|---------------------------------------------------|-----------------------------------------------------------------------------------------------------------------------------------------------------------------------------------------------------------------------------------------------------------------------------------------------|
| Email                                             | [REDACTED]                                                                                                                                                                                                                                                                                    |
| Reporting process                                 | Complete and sign the SAE Report Form within 24 h after being informed of any SAE and sends the form in PDF format to the sponsor's email [REDACTED] CRO Pharmacovigilance Public email [REDACTED]                                                                                            |
| Mail title                                        | Protocol No.-Site No.+Site name-First/Follow-up#/Summary-Random No.-SAE description-Severity criteria-Relatedness-Date the investigator was informed of this information.
E.g. GL-GLP-CH2005-01**Hospital-First-F001-Allergic reaction-Prolonged hospitalization-Unlikely related-20230310 |
| Reporting of pregnancies (24 h)            |                                                                                                                                                                                                                                                                                               |
| Email                                             | [REDACTED]                                                                                                                                                                                                                                                                                    |
| Reporting process                                 | The investigator completes and signs the Form for Pregnancy Report within 24 h after being informed of any pregnancy and sends the form in PDF format to the sponsor's email [REDACTED] CRO Pharmacovigilance Public email [REDACTED]                                                         |
| Mail title                                        | Protocol No.-Site No.+Site name-First/Follow-up#/Summary-Subject No.-Pregnancy-Date the investigator was informed of this information
E.g.: GL-GLP-CH2005-01**Hospital-First-F001-Pregnancy-20230310                                                                                       |

### **Adverse event code**

Encode all adverse events (severe and non-severe) using MedDRA (current effective version).

### **Treatment and follow-up of AEs**

Any AE occurring during the trial will be treated according to medical practice. All AEs should be followed up until the subject is recovered/resolved, recovering to stable status, recovered/resolved with sequelae, dead, or lost to follow-up.

Any AE continuing in the subject at the end of the study should be followed up until the subject is recovered from the event/recovered with sequelae and the sequelae remain stable, or until the investigator considers the event no longer clinically significant, or until the subject is lost to follow-up. If follow-up is not performed, the investigator must provide justification.

### **Pregnancy records and follow-up visit**

If the investigator finds that the subject became pregnant within 4 weeks after signing the ICF and the last medication, the investigator must fill out a pregnancy event report form

and provide it to the PV department of Gan & Lee Pharmaceutical (or its authorized CRO) within 24 hours. After confirming pregnancy (positive pregnancy test), the subject should withdraw from the study and complete the following activities:

- The subjects should return for early termination (ET) visits.
- The subjects should immediately stop using IMP.
- A safety visit should be planned 2 weeks after the subject terminates IMP treatment.

The investigator must inform the subjects of the current known potential risks and existing alternative treatments.

Pregnancy events should be recorded in the pregnancy event report form provided to the investigator. Pregnancy report forms must be used to track pregnancy progress and final childbirth (when applicable), and investigators must report the health status of the mother and child. Every effort should be made to follow up on the health status of the baby within 30 days after birth to determine if there are any significant medical issues. In some cases, Gan & Lee Pharmaceuticals may require continuous follow-up for more than 30 days. If the subject is lost to follow-up and/or refuses to provide information, the investigator shall provide written records of attempts to contact the subject and keep them on file at the research center. The PV department of Gan & Lee Pharmaceuticals /CRO is the primary contact person responsible for any issues related to pregnancy, final birth, and follow-up data collection.

If a partner of a male subject enrolled in a clinical study becomes pregnant, the investigator or designee is requested to contact the subject and ask the partner of the subject to sign a partner pregnancy consent form approved by relevant IRB/IEC and include this form in the study site file. If there is any objection to the informed consent process, the investigator may contact the CRA of Gan & Lee/CRO. Only after the partner has consented to the collection of additional information and provided a signed partner pregnancy consent form, the pregnancy report form will be completed by the investigator and sent to the PV Department of Gan & Lee/CRO (see SAE reporting information at the beginning of this protocol for contact information). The PV Department of Gan & Lee/CRO is also the primary point of contact for any questions related to the partner pregnancy, final birth and follow-up data collection.

If the following situations occur, pregnancy events are recorded as serious adverse event (SAE): miscarriage, miscarriage (elective or spontaneous), ectopic pregnancy, stillbirth, or any congenital abnormalities/birth defects in the baby. These SAEs must be

reported separately using the SAE report form. Selective induced abortion without medical reasons to terminate pregnancy is not considered an AE/SAE.

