  - ✓ Dose group 4 (s.c. 48 mg once every two weeks): Within 1 hour before the first administration (W0D0); within 1 hour of the first administration (W14) of the previous dose of the target dose; Within 1 hour before reaching the target dose for administration (W18); within 1 hour before administration at W26; within 1 hour before the 6th administration of the target dose (W28) and 72 hours  $\pm$  1 hour after administration; blood samples are collected in the morning of the end of study visit (W30). There are a total of 7 blood sampling time points.
  - ✓ Dose group 5 (s.c. 24 mg (18 mg)\*once-weekly): Within 1 hour before the first administration (W0D0); Within 1 hour before the first administration (W14) of the previous dose of the target dose; Within 1 hour before reaching the target dose for administration (W18); Within 1 hour before the 6th administration of the target dose (W23) and 72 hours  $\pm$  1 hour after administration; Within 1 hour before administration at W26 and W29; Blood samples are collected in the morning of the end of study visit (W30). There are a total of 8 blood sampling time points.
  - Time points of intensive blood sampling (not shown in the flowchart): Dose group 1 to 4 (GZR18 s.c. once every two weeks): Blood samples are collected within 1 hour before the last administration at W28 (coinciding with the sparse blood sampling time point W28 before administration, no need to repeat collection), 1 hour, 6 hours, 24 hours, 48 hours, 72 hours after administration (the group receiving only 24 mg and 48 mg once every two weeks coincides with the sparse blood sampling time point at W28 72 hours after administration, so there is no need to repeat the collection), 96 hours, 120 hours, 168 hours, 240 hours, 336 hours (coinciding with the sparse blood sampling time point at W30 after administration, no need to repeat collection), and 504 hours (W31). Dose group 5 (GZR18 s.c. once-weekly) Blood samples are collected within 1 hour before the last administration at W29 (overlapping with the sparse blood sampling time point at W29 before administration, no need to repeat collection), and 1 hour, 6 hours, 24 hours, 48 hours, 72 hours, 96 hours, 120 hours, 168 hours after administration (overlapping with the sparse blood sampling time point at W30, no need to repeat collection), 240 hours, 336 hours (W31), and 504 hours (W32).

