#### **4.1.1 Study duration for each subject**

- The maximum study period for each subject in this study is approximately 34 weeks: including a screening period of 1 week (Week -1), an administration treatment period/study visit of 30 weeks (Weeks 0 to 30, dose adjustment of weeks 10 to 18, stable dosage treatment period of 12 to 20 weeks) + safety follow-up of 3 weeks (Weeks 31 to 33).

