### 5.2 Exclusion criteria

Subjects will not be enrolled in the study if they meet any of the following criteria:

1. Limb deformities or defects affecting height and body weight measurement.
2. Pregnant or lactating women, men or women of reproductive potential unwilling to use contraception throughout the study and for 6 months after the last dose of investigational drug.
3. History of drug abuse within 1 year before screening, or positive results in drug abuse screening during screening or before randomization.
4. Alcohol abuse history, defined as an average weekly alcohol consumption of more than 14 units for men/7 units for women (1 standard unit equivalent to 360 mL of beer or 150 mL of wine or 45 mL of spirits with 40% alcohol) within 6 months prior to screening.
5. Subjects who are known or suspected to be allergic to GLP-1 drugs or excipients.
6. Subjects with an absolute weight change greater than 5.0% due to any reason within the 3 months prior to screening. The formula for calculating weight change is:  $(\text{highest weight in the 12 weeks prior to screening} - \text{lowest weight}) / \text{highest weight} * 100\%$ .
7. History or evidence of any of the following:
  - 1) Previous diagnosis of type 1 or type 2 diabetes mellitus;

- 
- 2) Proliferative retinopathy within 1 year prior to screening or at screening;
  - 3) Previous severe hypoglycemia or recurrent symptomatic hypoglycemia ( $\geq 2$  episodes in half a year);
  - 4) Secondary diseases or drugs leading to obesity, including: elevated cortisol (e.g. Cushing's syndrome), pituitary and hypothalamic damage leading to obesity, weight loss medicine reduction/discontinuation leading to obesity, etc;
  - 5) Previous history of moderate to severe depression; or previous history of severe psychiatric disorders, such as schizophrenia, bipolar disorder, etc. Or when screening, the score of Patient Health Questionnaire (PHQ-9)  $\geq 15$ ;
  - 6) Previous suicidal tendency or suicidal behaviour, or when screening, the subjects had suicidal ideation in categories 4 and 5 of the Columbia-Suicide Severity Rating Scale (C-SSRS);
  - 7) Systolic blood pressure  $\geq 160$  mmHg and/or diastolic blood pressure  $\geq 100$  mmHg at screening;

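### Section 7.4 ties the mandatory pregnancy report to 4 weeks after the last dose, but exclusion criterion 2 sets 6 months of contraception and other parts of 7.4 set no limit; the windows need reconciling

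*Protocol*

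**What the plan says.** Four parts of the protocol bear on this.

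- **Exclusion criterion 2 (sections 1.1 and 5.2)** excludes "men or women of reproductive potential unwilling to use contraception throughout the study and for 6 months after the last dose of investigational drug". It applies to both sexes and reaches 6 months past the last dose.
- **Section 7.4, Pregnancy records and follow-up visit** sets the trigger: where the subject "became pregnant within 4 weeks after signing the ICF and the last medication, the investigator must fill out a pregnancy event report form". The later duties in that section hang on this report: tracking the pregnancy to delivery, reporting the health of mother and child, and following the infant for 30 days. A separate paragraph opens with "If a partner of a male subject enrolled in a clinical study becomes pregnant" and requires a form once the partner has consented. It gives no start or end date. The section also classes pregnancy losses and birth defects as serious adverse events.
- **Section 7.4, Adverse event reporting** contains a table that asks the investigator to send the pregnancy form within 24 hours of learning of any pregnancy. It sets no period. The text before the table collects serious adverse events up to 4 weeks after the last dose, and those thought to be drug-related at any time.
- **Sections 1.2 and 4.1.1** fix the last contact. The last dose is at W28 in groups 1 to 4 ("Blood samples are collected within 1 hour before the last administration at W28") and at W29 in group 5 ("Blood samples are collected within 1 hour before the last administration at W29"). Follow-up is a "safety follow-up of 3 weeks (Weeks 31 to 33"), and the last scheduled pregnancy test is at W33 or at the early termination visit.

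**The concern.** The protocol asks subjects to avoid pregnancy for 6 months after dosing, but the clause that obliges sites to report and follow a pregnancy stops at 4 weeks. No reason is given for the shorter period. A subject who conceives 6 weeks after her last dose is inside the contraception period and outside the clause that leads to outcome and infant follow-up.

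The clause is also hard to apply. Its wording has no clear start and could be read as 4 weeks after consent. The reporting table in the same section, read alone, has no limit at all. Two sites could handle the same pregnancy differently and each point to the protocol.

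What is at stake is how complete the pregnancy-outcome data are. Such events will probably be few, so each outcome that is missed matters. No efficacy result depends on it.

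**Working it through.** No figure in the protocol is being reproduced here. The check compares time windows.

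**Inputs**
- Contraception period after the last dose: 6 months (5.2, criterion 2). The protocol does not convert this to weeks. I take 26 weeks and show 25.7 (180 days) to 26.1 (182.6 days).
- Reporting trigger: 4 weeks after the last dose (7.4), on the sensible reading of the sentence.
- Last dose: W28 = D196 (groups 1 to 4), W29 = D203 (group 5). Last visit: W33 = D231 (1.2 and 1.3).

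**1. Share of the post-dose contraception period outside the 4-week trigger (female subjects)**
- Uncovered weeks = 26 − 4 = 22.
- Share = 22 / 26 = 0.846, about 85%.
- Range: 21.7 / 25.7 = 0.844 to 22.1 / 26.1 = 0.847.

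**2. Does scheduled contact extend the coverage?**
- Groups 1 to 4: 231 − 196 = 35 days = 5 weeks, leaving (26 − 5) / 26 = 0.808, about 81%.
- Group 5: 231 − 203 = 28 days = 4 weeks, leaving (26 − 4) / 26 = 0.846, about 85%.
- These are nominal days. The visit windows (±2 days at the last dose, ±3 days at W33) can move either interval by up to 5 days.
- For early withdrawals, the flowchart shows no pregnancy test after the early termination visit.

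Scheduled contact therefore adds at most about a week to the 4-week trigger.

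**3. Against the whole contraception period, W0 to 6 months after the last dose**
- Groups 1 to 4: 22 / (28 + 26) = 22 / 54 = 0.407.
- Group 5: 22 / (29 + 26) = 22 / 55 = 0.400.

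So about 40% of the whole period is uncovered. The 85% describes the post-dose 6 months only.

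**4. The clauses side by side**

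| Clause | Who | End of window |
|---|---|---|
| Exclusion criterion 2 (contraception) | men and women | 6 months after last dose |
| 7.4, pregnancy report trigger | subject who becomes pregnant | 4 weeks after last medication (garbled) |
| 7.4, reporting table | any pregnancy the site learns of | none stated |
| 7.4, partner paragraph | partners of male subjects | none stated |
| 7.4, serious adverse events | all subjects | 4 weeks after last dose; none if thought related |

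The trigger and the table give different answers for a conception after week 4. Neither they nor the partner paragraph provides a way of finding out about one after W33.

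**The case against.** A reader might infer that sites have no duty to report a pregnancy beginning after 4 weeks, or that losses and birth defects in that period could never reach the sponsor. The text does not support either. The reporting table requires a form whenever a site is told of a pregnancy. Serious adverse events judged related are reportable at any time, and 7.4 counts losses and birth defects among serious adverse events. Partner pregnancies carry no 4-week limit, so the 85% cannot be applied to them.

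It is also fair to say that criterion 2 is an eligibility rule about willingness to use contraception. The protocol does not call the 6 months a fetal-exposure period or give a reason for its length, and it may be precautionary. No half-life for GZR18 is stated; half-life is an endpoint of this trial. The 4 weeks match the general window for serious adverse events and may have been chosen for that reason. The 85% is a share of calendar time. It is not a share of pregnancies or of drug exposure, and the protocol gives no basis for an expected number of pregnancies. The garbled sentence looks like a translation fault, since the serious adverse event sentence has the same construction.

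All of this limits the claim but leaves a gap. An unlimited duty to report what one is told does not make anyone ask, and no contact is scheduled after W33. If the table does mean no limit, it contradicts the trigger a few paragraphs later.

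**Conclusion.** The point holds as an inconsistency with a practical gap behind it. For female subjects, about 22 of the 26 weeks after the last dose (85%, or 81% to 85% when counted to the nominal W33 visit) fall outside the clause or visit schedule that would reliably pick up a pregnancy. Pregnancies in that time would come to light through chance notification or a related serious adverse event. For partners, the fault is that no window is stated.

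This rests on three assumptions: 6 months is about 26 weeks, the trigger runs from consent to 4 weeks after the last dose, and subjects follow the nominal schedule. The documents do not show which of the two durations is right, and this review takes no position on it. The sponsor should make the change as a low-cost improvement to safety reporting. The primary analysis, the sample size of 338 and the on-treatment safety data do not depend on it.

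**What to change.** Reconcile exclusion criterion 2 (1.1 and 5.2) with the pregnancy section, the partner paragraph and the reporting table in 7.4:

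1. State one collection window for pregnancies in subjects and in partners of male subjects. It should run from consent to the end of whatever post-dose contraception period the sponsor confirms and justifies.
2. Rewrite the trigger sentence so that its start and end are unambiguous, and make the reporting table refer to the same window.
3. At W33 or early termination, tell subjects to report any pregnancy, their own or a partner's, that begins within that window.

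The cost is a few sentences in 7.4, a line in the consent form, and a safety database kept open longer for pregnancy reports only. No extra visit is needed. A telephone check at the end of the window would be optional.
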